Therefore, presurgery weight loss offers potential benefits and drawbacks that may be dependent on the actual body composition changes that occur; lower fat mass might be beneficial for reducing surgical complications, but reduced muscle mass is likely detrimental for overall morbidity and mortality. Until the effects of preoperative weight loss are better understood, it may not be appropriate to encourage patients to lose weight.^22^ A greater understanding of these factors would help to generate evidence-based recommendations for cancer patients providing much needed guidance for dietitians and specialist exercise professionals working with people affected by cancer.

Current recommendations advocate for prehabilitation programmes for cancer patients,^23^ which is the use of targeted interventions between the time of diagnosis and acute treatment to promote health and reduce the risk of future impairments.^24^ Prehabilitation interventions including exercise, nutrition and psychological support (either alone or in combination) have been shown to improve patient outcomes such as surgical complications, length of hospital stay and quality of life compared with usual care, and thus should be considered in standard care.^25^ Indeed, the National Cancer Plan for England acknowledges the importance of cancer prehabilitation and sets out the ambition to deliver a national ‘digital first’ prehabilitation offer by 2028.^26^ Therefore, investigating the effects of preoperative weight loss within a prehabilitation service will provide valuable information that could benefit individuals within this type of service.

Active Together is a multimodal prehabilitation and rehabilitation service in South Yorkshire, UK, which provides support to cancer patients to prepare for and recover from treatment.^27^ The service, which was co-designed by cancer patients, clinicians, professionals and academics, provides exercise, nutrition and psychological support to patients throughout the cancer care journey, spanning from prehabilitation before and during treatment to restorative and supportive rehabilitation after treatment.^28^ Patients are referred to the service after diagnosis where they undergo assessments to ascertain their physical, nutritional and psychological status, before receiving person-centred support underpinned by behaviour change techniques.^28^

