### Procedures

#### Primary data

Participants will be required to attend the Advanced Wellbeing Research Centre (AWRC) at Sheffield Hallam University on two separate occasions. The first visit will take place as soon as possible after diagnosis, during which participants will complete two questionnaires and four physical assessments. On arriving at the AWRC, participants will be greeted by a member of the research team and taken to the morphology lab where they will be seated in a neutral space with no sight of the equipment. The researcher will explain the study again and provide an opportunity to ask any questions before the participant provides their informed consent to participate.

Participants will then be asked to complete the following questionnaires: the EuroQol 5-Dimensions 5-Levels (EQ-5D-5L) to measure quality of life^29^ and the Patient Generated Subjective Global Assessment Short Form (PG-SGA-SF) to measure nutritional status.^30 31^ Next, participants will be asked to void their bladder, change into form-fitting, non-compressive clothing, and remove all jewellery to complete the four physical assessments: stature (Seca 264, Seca, Germany), body mass and body composition (proportions of fat and fat-free mass) using a BOD POD (Cosmed, Italy) and body size and shape (including waist, upper arm, and calf circumference) using the Size Stream SS20 3D body scanner (Size Stream, NC, USA). The second visit will take place within the 2 weeks prior to the participant having surgery, and the data collection for this visit will be the same as visit one, with the addition of another questionnaire to gather information on participants’ weight loss intentions, strategies and advice received; see online supplemental material 1.

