Separate linear regression models will be created to investigate the amount of variation in self-reported and clinical outcomes which are explained by preoperative changes in patient body measures. Then, multivariate regression models will be created which combine patient outcome measures that contribute significantly to the estimation of clinical outcomes. Ordinal logistic regression models will also be used to explore the relationship between patient outcome measures and ordinal clinical outcome variables, such as surgical complications (Clavien-Dindo classification) and the surgical approach used. Where the distribution of data indicates it would be appropriate (ie, for non-linear relationships between predictor and outcome variables), other regression approaches such as restricted cubic splines or generalised additive models will be used. Regression analyses are appropriate as this is exploratory research, and this approach allows the observation of relationships between all variables. The regression models will all be adjusted for the variability in time between the assessment points, tumour group and pretreatment therapies where these are shown to reduce residual variance and not introduce collinearity to the model. Any outliers will be investigated to ensure that they are legitimate observations; only implausible data will be removed.

Multiple regression models will be assessed for multicollinearity between input variables using variance inflation factor and tolerance collinearity statistics and for independence of errors using the Durbin-Watson test statistic. If the largest variance inflation factor value is >10, or tolerance values are below 0.2 this could indicate potential issues in the model associated with multicollinearity. Also, if Durbin-Watson values differed significantly from two this would suggest dependence of errors between input variables in the model. Additionally, regression assumptions (eg, homoscedasticity, normally distributed errors) will be checked via diagnostic plots, and transformations of variables will be used if assumptions are not met.

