Data from the Active Together service shows that many patients are unable to attend assessment appointments prior to surgery, often due to short notice of surgery dates. This might lead to missing data at the presurgery assessment point (visit 2). All efforts will be made to make attending appointments as convenient as possible for patients. Additionally, patients are routinely weighed before surgery; therefore, the key outcomes of body mass change and surgical outcomes should always be available. Therefore, statistical analyses for body mass change will include all participants, and analyses including body composition, size and shape, and questionnaire data will be performed on a smaller cohort if some data are missing.

Complete case analyses will be performed when covariates (eg, body composition variables) contain missing data. Complete case analysis can lead to biased parameter estimates in regression models if the data are not missing completely at random (MCAR). Therefore, graphical techniques and Little’s hypothesis test of the MCAR assumption will be used to explore whether the MCAR assumption is a reasonable one to make with the collected data. If not, a standard multiple imputation method will be implemented (eg, Multiple Imputation by Chained Equations, Linear Regression Imputation or Predictive Mean Matching).

For linear regression analyses, assuming a medium effect size (F^2^=0.15), significance level=0.05, power=0.8 and number of predictors=6, a sample size of 98 is required.^33^ For correlation, assuming a two-tailed test, a medium effect size (rho=0.3), significance level=0.05 and power=0.8, a sample size of 84 is required.^33^ Therefore, a sample size of 100 participants is required to detect medium effect sizes with acceptable statistical power. Furthermore, 100 participants is a reasonable estimate of the number of potential participants within the study’s time frame based on the demographics of current and previous Active Together patients (ie, number of patients awaiting surgery for upper GI or colorectal cancer with a BMI ≥30 kg/m^2^).

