For the data collected through the weight loss intention, strategies and advice questionnaire, the number and proportion of responses for each question will be recorded and subgroup analyses performed depending on the responses, for example comparisons of surgical outcomes between those who lost weight intentionally, those who lost weight unintentionally and those who didn’t lose weight. The final question will be analysed using thematic analysis by manually identifying patterns and themes in the responses and will be reported narratively. Member checking will be undertaken by an independent qualitative researcher to check that the analysis is accurate and has not over-represented or under-represented any aspects of the data.

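### Weight-loss intention is not a listed adjuster, and the questionnaire that separates deliberate from unintentional loss is given only at the visit most likely to be missed

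*Protocol article*

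**What the plan says.** **Motivation.** The Introduction says that benefit or harm may depend on which tissue is lost and that about one in two people with cancer will experience cachexia. It concludes: "Until the effects of preoperative weight loss are better understood, it may not be appropriate to encourage patients to lose weight".

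**Main models.** Under Statistics and analysis the exposure is preoperative change in body measures, taken as a whole. On adjustment: "The regression models will all be adjusted for the variability in time between the assessment points, tumour group and pretreatment therapies", each kept only where it reduces residual variance without adding collinearity. Intention is not on that list.

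**Where intention is recorded.** Procedures (Primary data) adds one questionnaire at the second visit, on "weight loss intentions, strategies and advice received". No other source of intention is described, and neither is completion without an in-person session.

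**Where intention is used.** The end of Statistics and analysis gives, as an example of subgroup analyses, "comparisons of surgical outcomes between those who lost weight intentionally, those who lost weight unintentionally" and those who did not lose weight.

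**Expected attendance.** Service data show that "many patients are unable to attend assessment appointments prior to surgery, often due to short notice of surgery dates", and the protocol accepts that this might leave data missing at visit 2. Because patients are routinely weighed before surgery, mass-change analyses are to include all participants. Analyses of composition, size and questionnaire data use a smaller cohort where data are missing.

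**The concern.** By the protocol's own account, weight lost on purpose and weight lost through disease may relate differently to surgical outcome. A model that uses total mass change whatever its cause estimates a mixture of the two, weighted by how many patients of each kind were recruited. The subgroup comparison is the one place where the mixture is taken apart.

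That comparison depends on the data most exposed to loss. A patient called to surgery at short notice still contributes mass change and outcome, but not intention. Composition change, the other variable that could help to interpret the loss, also needs visit 2. Time to surgery varies with tumour location, waiting time and neo-adjuvant treatment (Study design), so those who attend may differ systematically from those who do not. Intention that is not recorded before surgery can later be obtained only by recall, once the outcome is known.

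**Working it through.** **1. The protocol's own sample sizes.** These are "assuming a medium effect size (F^2^=0.15), significance level=0.05, power=0.8 and number of predictors=6, a sample size of 98 is required" and "assuming a two-tailed test, a medium effect size (rho=0.3), significance level=0.05 and power=0.8, a sample size of 84 is required".
- Regression, overall F test with λ = f²·N = 0.15 × 98 = 14.7 on 6 and 91 degrees of freedom: power 0.804. N = 98 is reproduced.
- Correlation, Fisher z: ((1.960 + 0.842)/atanh 0.3)² + 3 = 84.9. The exact distribution of r gives power 0.801 at N = 84. This is reproduced.

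Neither calculation covers the intentional versus unintentional contrast, and neither allows for missed visits.

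**2. Loss of intention data.** The protocol gives no rate. If 20% to 40% miss visit 2 (assumed), intention is unknown in 100 × 0.20 = 20 to 100 × 0.40 = 40 participants who still have mass change and outcome. That leaves 80 to 60 questionnaires.

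**3. Effect on the intention comparison.** Group shares are also not given. I take intentional/unintentional shares of 25%/15% and 33%/33% as assumed cases.
- Power for a difference of d standard deviations (SD): Φ(d/√(1/n₁ + 1/n₂) − 1.960), with d = 0.5 assumed.
- Difference detectable at 80% power: (1.960 + 0.842) × √(1/n₁ + 1/n₂).
- Complications: 15% v 30% (assumed, with 15% in the intentional group), two-proportion normal approximation.

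| Questionnaires | Shares | n₁, n₂ | Power, 0.5 SD | Detectable difference (SD) | Power, 15% v 30% |
|---|---|---|---|---|---|
| 100 | 25/15 | 25, 15 | 0.334 | 0.91 | 0.215 |
| 100 | 33/33 | 33, 33 | 0.528 | 0.69 | 0.305 |
| 80 | 25/15 | 20, 12 | 0.277 | 1.02 | 0.183 |
| 80 | 33/33 | 26.4, 26.4 | 0.443 | 0.77 | 0.253 |
| 60 | 25/15 | 15, 9 | 0.219 | 1.18 | 0.151 |
| 60 | 33/33 | 19.8, 19.8 | 0.349 | 0.89 | 0.199 |

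For 80% power, 0.5 SD needs 63 per group and 15% v 30% needs 121 per group. The comparison is imprecise even with every questionnaire returned, and missed visits make it more so.

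**4. Adding intention to the main models instead.** Intention as a three-level factor adds two terms. With 8 predictors, the protocol's overall-F method requires 109 rather than 98, and gives power 0.76 at N = 100. For two intention-by-change terms (10 predictors, 2 tested):

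| Partial f² | Power, 100 questionnaires | Power, 60 questionnaires |
|---|---|---|
| 0.15 | 0.94 | 0.74 |
| 0.05 | 0.49 | 0.30 |
| 0.02 | 0.22 | 0.14 |

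**5. Why the pooled association needs care.** Illustration with assumed complication risks: no loss 30%, deliberate loss 20%, unintentional loss 45%. Pooled risk among losers is p × 0.20 + (1 − p) × 0.45, where p is the deliberate share. This gives 27.5% at p = 0.7, 32.5% at p = 0.5 and 37.5% at p = 0.3. The sign relative to 30% follows case mix because opposite effects were put in. It shows what could happen and is not evidence that it will.

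**The case against.** A reader might infer that the study cannot say anything about whether losing weight on advice helps or harms. The documents do not support that. The protocol plans the three-way comparison and records advice received, so it can describe the contrast, though imprecisely. The stated aim is association, the work is called exploratory, and the strengths and limitations list disclaims causal inference. Better questionnaire return would not change the causal limit.

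Other points on that side:
- **Attendance.** The protocol says only that data might be missing at visit 2, promises efforts to make attendance convenient, and offers sessions where patients already attend the service. This stands, and the rate is unknown. Those sessions are still in person, however.
- **Composition and nutrition.** The protocol's own explanation turns on the tissue lost, and composition change is among the modelled exposures. EQ-5D-5L and PG-SGA-SF are also collected by the prehabilitation service. This stands in part: none of these measures intention, and composition is lost with the same missed visit.
- **Unseen graphs.** Directed acyclic graphs are said to decide adjustment and are not shown, so intention may appear in them. The listed adjusters nevertheless omit it.
- **Missing-data plan.** Multiple imputation is available for covariates if data do not look missing completely at random. Intention is not a listed covariate, and a recorded answer is better than an imputed one.
- **Detail.** An article need not state the adjustment of one example subgroup comparison, so its absence is not counted here as a fault.

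**Conclusion.** The point holds as a cheap improvement to data collection and reporting. From the text: the listed adjusters omit intention, the only described measure of it is tied to attendance at visit 2, and patients who miss that visit remain in the mass-change analysis. Their intention would be unknown, and the intention comparison would rest on a smaller, possibly selected cohort.

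The size is conditional. The missed-visit rate, group shares, effect sizes and complication risks above are all assumptions. Across the cases shown, falling from 100 to 60 questionnaires lowers power for half a standard deviation from 0.33–0.53 to 0.22–0.35. Selection could matter more than the loss of precision, but the documents give nothing from which to size it.

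It would go too far to say that intention must enter the main models. At this sample size that is a trade-off: power for an interaction is low unless the effect is at least medium. A two-level deliberate/not deliberate coding would also leave patients who lost no weight without a clear place, so the planned three-group comparison is the clearer contrast.

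**What to change.** 1. **Procedures, Primary data.** When visit 2 cannot take place, allow the intention questionnaire, and with it the EQ-5D-5L and PG-SGA-SF, to be completed by telephone, post or online before surgery. Record the mode and the date.
2. **Statistics and analysis, subgroup paragraph.** Keep the comparison of intentional loss, unintentional loss and no loss. Report it as estimates with confidence intervals, using the adjusters named for the regression models where numbers allow. Report how many participants in the mass-change analysis have unknown intention.
3. **Statistics and analysis, main models.** State that the pooled mass-change association should not be read as the effect of advised weight loss.
4. **Optional.** An intention-by-change interaction may be fitted and labelled exploratory, with within-group slopes and intervals.

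Cost: a minor amendment, a few minutes per missed visit, and mixed completion modes, which recording the mode makes visible. No change to sample size is needed, because the comparison would be reported as estimation and not as a powered test.

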### Ethics and dissemination

The Principal Investigator will ensure that this study is conducted in accordance with the principles of the Declaration of Helsinki, relevant regulations and with Good Clinical Practice. This study has been approved by the Health Research Authority (Integrated Research Application System project ID 361634; Research Ethics Committee reference 26/YH/0019). The Principal Investigator will submit and, where necessary, obtain approval from the Health Research Authority for any amendments to the original approved documents.

Prospective participants will be provided with a copy of the Participant Information Sheet which details the nature of the study, what will be required of them, the benefits and risks of their participation and information on how their data will be used. Written informed consent will be provided by all participants at the start of their first visit for the study, before any study-related procedures take place. This will be obtained in the form of a participant-signed and dated informed consent form, including the dated signature of the person obtaining informed consent. The Participant Information Sheet and all other participant-facing documentation has been scrutinised and deemed appropriate by the Public and Patient Involvement steering committee.

A participant may choose to withdraw early from the study at any time. If a participant withdraws from the study before their second visit or surgery, their data will also be removed from the study dataset as both visits and surgical data are required to answer the research questions. If a participant withdraws from the study after their surgery, no further data will be collected from their records (surgical or Active Together outcomes) for the study, but data that has already been collected (ie, from surgery and the two data collection sessions) will be used for analysis. Participants will be made aware of their right to withdraw and what happens to their data on withdrawal via the Participant Information Sheet and give consent to this on the Informed Consent Form.

Data will be input into spreadsheets by the research team and held on a secure research drive by Sheffield Hallam University. Sheffield Hallam University policy requires study data to be archived for 5 years; this will be made clear on the Participant Information Sheet, and participants will consent to storing data in this way in the Informed Consent Form. Participants will also be asked for their consent for their anonymised data to be stored in the Sheffield Hallam University Research Data Archive (SHURDA) database for a period of 10 years since the last time any third party has requested access to the data. If participants do not consent to this, their data will not be uploaded to SHURDA and will be destroyed after 5 years.

The study will comply with the General Data Protection Regulation and Data Protection Act 2018, which require data to be deidentified as soon as it is practical to do so. The processing of the personal data of participants will be minimised by using a unique participant study ID on all study documents and any electronic database(s). A password-protected ‘key’ file containing participant information and their study ID will be kept separate to all study documentation. All documents will be stored securely and only accessible by study staff and authorised personnel. The study staff will safeguard the privacy of participants’ personal data.

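### The reason given for deleting all data after withdrawal before visit 2 or surgery conflicts with the plan's own analyses, and the rule discards usable data

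*Protocol article*

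**What the plan says.** The withdrawal rule is in the protocol article under Ethics and dissemination. It applies to anyone who withdraws before surgery or before visit 2, and it says that "their data will also be removed from the study dataset as both visits and surgical data are required to answer the research questions". Rule and reason stand in one sentence. For withdrawal after surgery the same paragraph does the opposite: collection stops, but what has already been collected is analysed. Participants are told of these consequences in the information sheet and agree to them on the consent form.

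The Statistics and analysis section deals with participants who do not attend visit 2. It expects this to be common, since "many patients are unable to attend assessment appointments prior to surgery, often due to short notice of surgery dates". It then says that "patients are routinely weighed before surgery; therefore, the key outcomes of body mass change and surgical outcomes should always be available", that "statistical analyses for body mass change will include all participants", and that "analyses including body composition, size and shape, and questionnaire data will be performed on a smaller cohort if some data are missing". Complete-case analysis is the starting point. Graphical checks and Little's test are used to judge whether data are missing completely at random (MCAR), and multiple imputation follows if they are not.

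The aim, stated at the end of the Introduction, relates preoperative changes in body mass and composition to four groups of outcomes: surgical outcomes, physical fitness, nutritional status and quality of life. The Statistics and analysis section mentions a separate causal graph for preoperative well-being in the supplement.

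**The concern.** The deletion rule rests entirely on the claim that a participant without both visits and a surgical record cannot help to answer the research questions. If the rest of the plan shows that such participants can contribute, the rule throws away data for a reason the plan itself does not accept.

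Two things are at stake. The first is usable information, in a study with a recruitment target of 100. The second is the ability to see who left. Withdrawal between diagnosis and surgery may be related to health. If the visit 1 records of those who leave are deleted, nobody can later check whether they resembled those who stayed. The Statistics and analysis section itself warns that complete-case estimates can be biased when data are not MCAR. The withdrawal rule imposes a restriction of that kind outside the checks meant to detect the problem.

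**Working it through.** No arithmetic applies, because the article gives no withdrawal rate and no figure that depends on one. The check is to compare the stated reason with what each analysis needs.

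**Step 1: is visit 2 required?** For body composition, size and shape, and the visit 2 questionnaires, yes. For body mass change, no. The Statistics and analysis section substitutes the routine pre-surgery weight and takes surgical outcomes from hospital sources. It calls these the key outcomes and says of them: "the key outcomes of body mass change and surgical outcomes should always be available". The claim that both visits are needed is therefore not true of the analyses the plan treats as central.

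**Step 2: are surgical data required?** For associations with complications, operating time, length of stay, readmission and survival, yes. For associations of body change with preoperative nutritional status, quality of life and fitness, no. Visits 1 and 2 each collect body mass, body composition, the PG-SGA-SF and the EQ-5D-5L, and the Active Together service records fitness at its own assessments.

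**Step 3: apply the rule to each kind of participant.**

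- *Misses visit 2 without withdrawing.* Kept. Enters the body-mass-change analyses through the routine weight.
- *Withdraws before visit 2, but would allow use of records.* Deleted. Could supply visit 1 mass, the routine pre-surgery weight and surgical outcomes, which is the same information as the participant above.
- *Withdraws after visit 2 and before surgery.* Deleted. Has complete paired measurements of body mass, composition, nutritional status and quality of life, enough for the preoperative associations.
- *Withdraws before visit 2 and refuses further record use.* Deleted. Could supply only visit 1 data, which describe who left and can inform the missing-data work.
- *Withdraws after surgery.* Data already collected are kept.

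In the second and third cases the reason fails on the plan's own terms. In the fourth it holds for the main associations, but deletion still has a cost (step 4). The fifth shows that keeping data up to the point of withdrawal is already accepted in this study.

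**Step 4: effect on the missing-data plan.** The graphical checks, Little's test and imputation can use only participants who are in the dataset. A deleted participant does not appear as a record with visit 2 missing; there is no record at all. These methods therefore describe missingness only among those who did not withdraw before visit 2 or surgery, and visit 1 values of withdrawers cannot be set beside those of completers.

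**The case against.** The strongest reply is that the two sections concern different people. The Statistics and analysis section covers participants who miss visit 2, usually because surgery is scheduled at short notice; the withdrawal paragraph covers those who choose to leave. A participant who only misses visit 2 is not deleted. Deletion is also disclosed, consented to and part of an ethics-approved study. And someone who leaves before surgery and refuses record access has no surgical outcome in the study whatever is done with the visit 1 data. All of this stands. The conflict is between the stated reason and the analyses, not between two rules for the same person, and there is no ethical breach. The reply does not rescue the reason itself, nor the loss in the second and third cases above.

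A reader might be tempted to go further in four ways. The documents do not support them.

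- *That the rule removes sicker patients.* Nothing says who withdraws or why. The only cause given for missed appointments is logistical.
- *That it biases the main association by a known amount.* That would need an assumed withdrawal rate, an assumed dependence on later complications and an assumed sign. The Introduction cites fewer complications with greater loss in one trial and worse long-term outcomes in other work, so even the sign is open. Such a calculation would also measure the effect of withdrawal, most of which retaining visit 1 data would not undo.
- *That the plan to include all participants is untrue.* The phrase reads naturally as those still in the study.
- *That deletions push the study below its calculated sample size.* That is a question about attrition in general, since many withdrawers would lack the paired data in any case.

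**Conclusion.** The point holds in a limited form. The reason given for deletion is inconsistent with the Statistics and analysis section, where body mass change and surgical outcomes do not depend on visit 2, and with the stated aim, part of which does not depend on surgery. The rule therefore discards usable data from some withdrawers and prevents any examination of selection through withdrawal.

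The size cannot be stated. The number affected depends on a withdrawal rate the article does not give, and the direction and magnitude of any bias are unknown. The conclusion rests on two assumptions: that the phrase about withdrawing before the second visit or surgery covers someone who leaves between the two, which is its plain reading, and that some withdrawers would agree to continued use of their data or records. This is a cheap improvement worth making, not a flaw that undermines the study.

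**What to change.** 1. Remove the statement that both visits and surgical data are required, and bring the withdrawal paragraph into line with the Statistics and analysis section.
2. Offer two forms of withdrawal on the consent form: (a) stop study visits, but allow use of data already collected, the routine pre-surgery weight and hospital outcomes; or (b) stop all new collection, but keep data already collected, unless the participant asks for deletion.
3. Include participants who choose (a) in the body-mass-change analyses. Use the retained data of those who choose (b) wherever an analysis can take them, including the preoperative associations if they completed visit 2.
4. Report the number of withdrawers and, where consent allows, their visit 1 characteristics beside those of completers. Include their records in the MCAR check and any imputation.

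The cost is wording in the protocol, information sheet and consent form, with an ethics amendment. No extra visits or measurements are needed. It is best done early, because each participant is bound by the consent wording they signed and deleted data cannot be recovered.
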